#### Radiographic evaluation

3.1.13

Periapical and interproximal radiographs will be taken initially and immediately after the procedure. Subsequently, follow up will be performed at 3, 6, and 12 months for the evaluation of optical density on the radiographs and the visual clinical interpretation of the remaining dentin as well as the evaluation using the radiographic subtraction method.^[38]^ All radiographs will be performed with double film (Kodak).

For a better understanding of the radiographic subtraction method, the 4 radiographs will be compared and taken with minimal geometric distortion, which is achieved by individualizing the premanufactured film positioners based on occlusal records using self-curing acrylic resin specific for each patient. The positioners will be stored for the subsequent radiographs. Exposure time, kilowatts and milliamperes of the device, type of film and radiographic processing will be standardized to obtain the most identical density and contrast possible among the radiograph.^[39]^ The radiographic subtraction methods in dentistry first began to study arterial vascularization of the mandible and are currently employed in different specialties.^[39]^ A positioner for interproximal radiographs will be used. The acrylic resin will be placed on the tooth surface and its antagonist for the anatomic impression of these surfaces and adapted to the positioner.^[40]^ This will enable the same position of the film at the different evaluation times and the standardization of the same x-ray incidence, vertical and horizontal angles and distance for all radiographs of the same patient.^[40]^

The same development time, intermediate rinsing, fixation and final rinsing will be standardized for all evaluation periods. The dark room temperature will be the same and Kodak chemicals will be used. The radiographic images from the different evaluation times will be scanned for the analysis of differences in density. For such, the Imagelab 2.3 program will be used.^[38]^

The density of the remaining dentin will be based on the changes in optical density. The teeth submitted to restorative treatment in both groups will be reevaluated after 3, 6, and 12 months. This method will consist of analyzing the standardized and digitized periapical and interproximal radiographs of 48 teeth in 48 patients aged 7 to 10 years to determine quantitatively the gray tones in the affected dentin region immediately below the restoration in class ionomer cement, the radiographic control of which for the visualization of sound dentin will allow the clinical examiner to compare the density of the remaining dentin in the different groups. The statistical analysis of optical density will be performed using the mixed-effects model.

#### Evaluation of time required for procedure

3.1.14

The time required for each procedure will be measured using a digital stopwatch (Kenko, Hong Kong) in minutes and seconds from the onset of treatment until the complete removal of the carious tissue. The time will be recorded on a specific chart for analysis. The need or non-need for anesthesia will also be recorded.

#### Evaluation of need for local anesthesia during intervention and degree of pain/discomfort of children during procedure

3.1.15

All interventions will be initiated without the prior administration of local anesthesia. The children will be told that anesthesia could be administered at any time during the intervention. A face scale with different expressions will be used to evaluate the need for local anesthesia and the child will be asked to point to the expression that most corresponds to his/her degree of pain/discomfort.

Interpretation of face scale:

1.No pain.2.Mild pain.3.Moderate pain.4.A little worse pain.5.Strong pain.6.Worst pain.

#### Clinical evaluation

3.1.16

The clinical evaluation will be performed by researcher blinded to the different treatment groups. The criteria used of the evaluation will be the retention of the restorative material in the cavity and the occurrence of secondary caries. The evaluation scores will be based on the results of previous studies.^[4]^ Digital photographs of the restorations will also be taken and serve to complement the clinical and radiographic findings. The visual demonstration will contribute to any necessary clarifications and facilitate the discussion and documentation of the cases. Thus, digital photographs will be taken (camera: Canon Sx500 IS) of all teeth in the different groups before and after the interventions.

0 = present; no defects;1 = present; small marginal defects measuring less than 0.5 mm in depth; no need for repair;2 = present; small marginal defects measuring 0.5 mm to 1 mm in depth; need for repair;3 = present; large marginal defects measuring 1 or more mm in depth; need for repair;4 = absent; restoration nearly or completely lost; need for treatment;5 = absent; additional treatment having been performed for some reason;6 = tooth absent for any reason;7 = present; surface wear measuring less than 0.5 mm in depth; no need for replacement;8 = present; surface wear greater than 0.5 mm in depth; need for replacement;9 = impossible to diagnose.

#### Statistical analysis

3.1.17

The data will be analyzed statistically employing different tests and considering a 5% level of significance. The results will be submitted to descriptive analysis for the association of categorical variables in age and gender using the chi-square test and Fisher exact test. The Student *t* test and analysis of variance will be used for the comparison of means of the signs and symptoms of reversible pulpitis. Pearson correlation coefficients will be calculated to determine correlations among the continuous variables.

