#### Specific objectives

3.1.2

1.To compare photodynamic therapy with MB and PapacarieMBlue Papacarie^TM^ with regard to microbiological, radiographic, and clinical aspects.2.To evaluate the antimicrobial effect of aPDT on infected dentin in primary teeth.3.To perform a radiographic evaluation of the remaining dentin and radiographic density at 3 evaluation times over a 12-month period.

Hypothesis (H_1_): The administration of aPDT is effective in the treatment of infected carious dentin in primary teeth.

Hypothesis (H_0_): The administration of aPDT reduces the number of viable bacteria, but is not effective in the treatment of infected carious dentin in primary teeth.

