#### Sample size

3.1.8

The sample size will be calculated based on a previous study in the literature^[30]^ (Fig. 1), considering the expected difference and standard deviation and weighting colony forming units (CFU) of bacteria. For the statistical calculation, paired samples were considered, with *α* = 1.96 (5%); *β* = 0.84 (20%), and an 80% test power. The minimum number in this clinical trial was determined to be 16 teeth per group (Fig. 2).

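### The effectiveness hypothesis is tied to no outcome, contrast or time point, and the protocol's own pointers to a deciding outcome conflict

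*Protocol article*

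**What the plan says.** Section 3.1.2 (Specific objectives) sets out a comparison "with regard to microbiological, radiographic, and clinical aspects", without ranking the three. It then states H1: "The administration of aPDT is effective in the treatment of infected carious dentin in primary teeth". H1 names no comparator, measure or visit. The matching H0 grants that aPDT lowers the number of viable bacteria and denies only that it is effective treatment.

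Section 3.1.8 (Sample size) rests on bacterial counts, "considering the expected difference and standard deviation and weighting colony forming units (CFU) of bacteria", "with *α* = 1.96 (5%); *β* = 0.84 (20%), and an 80% test power". It adds: "For the statistical calculation, paired samples were considered". The result is stated as: "The minimum number in this clinical trial was determined to be 16 teeth per group". The text does not say which count was used.

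Section 3.1.12 lists six microbiological results: two counts and four proportions. Section 3.1.13 says "The teeth submitted to restorative treatment in both groups will be reevaluated after 3, 6, and 12 months" and assigns optical density to a mixed-effects model without naming the contrast to be read from it. The abstract puts clinical follow-up at the same three visits.

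Section 3.1.17 says "The data will be analyzed statistically employing different tests and considering a 5% level of significance". The only comparison of means it names is for reversible-pulpitis signs and symptoms. No outcome in the article is called primary, secondary or exploratory.

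**The concern.** H1 is a single yes-or-no claim, but nothing says which result answers it, and the sections that might imply an answer point in different directions:

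- The sample size points to CFU.
- H0 rules CFU out as the decider, because it already concedes a bacterial reduction.
- The analysis section points to reversible pulpitis, which none of the evaluation sections (3.1.12 to 3.1.16) describes how to measure.

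Two things are at stake. First, a favorable result on any aspect could be reported as support for H1, so the stated 5% level does not govern the trial's conclusion. Second, mixed results have no rule. They are plausible: section 3.1.7 has Group 1 remove carious dentin with burs, while Group 2 leaves the carious tissue on the pulp floor. Bacterial counts could therefore favor one group and a density reading the other. The 80% power was computed for CFU and may not apply to whichever result ends up deciding.

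**Working it through.** **The plan's own figure.** The constants 1.96 and 0.84 are the normal quantiles for two-sided 5% and 80% power (1.960 and 0.842). The expected difference and SD are not in the readable text (Figures 1 and 2 are not shown), so 16 per group cannot be reproduced from its inputs. Read as 16 pairs, it can be solved backwards: n = ((1.96 + 0.84) / d)² = 16 gives d = 2.80 / 4 = 0.70, the standardized paired difference in CFU. The sample size therefore supports one paired CFU contrast and says nothing about the other outcomes.

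**Where each section points.**

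| Section | Implied deciding outcome |
|---|---|
| 3.1.8 Sample size | CFU, count not specified |
| 3.1.2 H0 | Something other than bacterial reduction, which is conceded |
| 3.1.2 Objective 1 | Three aspects of equal rank |
| 3.1.17 Statistical analysis | Reversible-pulpitis signs and symptoms |

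**Size of the effect on error.** The article gives neither the number of tests nor their correlation. Three assumed families of tests:

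- 3 tests: one per aspect.
- 5 tests: one CFU result, one density test (the mixed model merging the visits), and the clinical score at three visits.
- 7 tests: one CFU result, and density and clinical score at three visits each.

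Only a rejection favoring aPDT supports H1. Each two-sided 5% test gives that with probability 0.025 when there is no true difference. For k independent tests the chance of at least one is 1 − 0.975^k:

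- k = 3: 1 − 0.975³ = 7.3%
- k = 5: 1 − 0.975⁵ = 11.9%
- k = 7: 1 − 0.975⁷ = 16.2%

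For rejection in either direction it is 1 − 0.95^k: 14.3%, 22.6% and 30.2%.

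For correlated tests, each statistic was simulated as √ρ·C + √(1−ρ)·E, with C a shared and E a separate standard normal, over 1,000,000 draws. Rejection was beyond 1.96 (favoring aPDT) or beyond ±1.96 (either direction).

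| Tests | Favoring aPDT, ρ = 0 / 0.5 / 0.8 | Either direction, ρ = 0 / 0.5 / 0.8 |
|---|---|---|
| 3 | 7.3% / 6.3% / 4.9% | 14.3% / 12.5% / 9.8% |
| 5 | 11.9% / 9.2% / 6.3% | 22.6% / 18.3% / 12.7% |
| 7 | 16.2% / 11.5% / 7.4% | 30.2% / 23.0% / 14.9% |
| Nominal | 2.5% | 5% |

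At ρ = 0.5 the risk of a false result favoring aPDT is 6.3 / 2.5 = 2.5, 9.2 / 2.5 = 3.7 and 11.5 / 2.5 = 4.6 times nominal. With one named contrast it returns to 2.5% (5% in either direction).

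**The case against.** The strongest reply is that this is a condensed article: hierarchies, alpha splits and exploratory labels commonly sit in an analysis plan, and CFU, as the powered outcome, is the implied primary. The first part stands, and the absence of such labels would not by itself be a finding. The second part does not stand. The count is not identified, nothing links H1 to it, and H0 as worded excludes it. An analysis plan details the outcome that the protocol has chosen; it cannot resolve hypotheses and a sample size that disagree about which outcome that is.

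Several stronger readings are tempting but not supported:

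- A reader might infer that a false claim of effectiveness is several times likelier than 5%. That counts rejections against aPDT, which do not support H1. Measured against 5%, the one-direction risk at ρ = 0.5 is 1.3, 1.8 and 2.3 times for 3, 5 and 7 tests. The multiples of 2.5 to 4.6 apply only against the nominal 2.5%.
- A reader might count procedure time, pain and anesthesia as further chances to support H1. Sections 3.1.14 and 3.1.15 record them, but no objective or hypothesis names them.
- A reader might count all six microbiological results as separate chances. The proportions share numerators and denominators, so treating them as independent overstates the risk.
- A reader might insist on three separate density tests. The planned mixed model may give one, which is why the five-test family is shown.

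It is also fair that 3.1.17 does not spell out a 5% test for each outcome and visit. That all aspects are eligible is a reading of one general sentence together with unranked objectives, so the error rates are conditional on that reading.

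**Conclusion.** The point holds as a conflict within the stated protocol text. H1 has no deciding outcome, contrast or time point, and the sample size, H0 and the analysis section imply different ones. If any one aspect may support H1, the chance of a false result favoring aPDT is about 6% to 12% for 3 to 7 tests at a correlation of 0.5, against a nominal 2.5%. It ranges from about 5% to 16% over correlations from 0.8 to 0. Those figures rest on assumed correlations and test counts and on two-sided 5% tests with no true difference. The conflict itself needs no such assumption: as worded, even a clear CFU result would leave H1 and H0 undistinguished.

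**What to change.** Three changes, made together:

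1. In 3.1.17, name one deciding contrast at two-sided 5%: Group 2 versus Group 1 in the change in log10 CFU from before to after treatment, for the count used in the sample size calculation, analysed as paired. The sponsor must state which count that is. Section 3.1.13 speaks of 48 teeth in 48 patients, which does not fit pairing within a child or 32 teeth, and should be reconciled at the same time.
2. In 3.1.2, reword H0 and H1 to match that contrast, with H0 as no difference between groups, so that the null no longer concedes a bacterial reduction. Without this step, naming CFU would leave H1 decided by something H0 already grants.
3. Label the other microbiological results, the radiographic and clinical results, and time, pain and anesthesia as secondary or exploratory. Report them with estimates and 95% confidence intervals, and do not use them to accept H1.

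The cost is a few sentences, with no extra teeth, visits or assays. The downside is that a favorable radiographic or clinical result could no longer support H1 by itself, and the conclusion on H1 would be limited to the antimicrobial effect. If the sponsor prefers to keep seven contrasts eligible, testing each at 0.05 / 7 = 0.0071 holds the either-direction risk at 4.9% for independent tests, at a cost in power for each; the hypotheses would still need rewording.

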#### Exclusion criteria

3.1.6

1.Systemic adverse health condition;2.Uncooperative behavior;3.Class II, III, IV, or V carious lesion based on Black classification;4.Clinically: caries involving enamel, deficient restorations, small carious lesions on dentin with no access for manual scalers, hidden caries, sign or symptom of pulp involvement, clinical impossibility of restoration;5.Radiographically: evidence of pulp involvement, carious lesion extending beyond 2/3 of dentin.

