#### Microbiological evaluation

3.1.12

A sample of infected dentin will be taken from each selected tooth before the removal of the carious tissue. The samples will be standardized with the use of a Meyhoefer auricular curette n° 2 and placed into test tubes containing 3.8 ml of transport medium (phosphate buffered saline; Labcenter, São Paulo, Brazil). The dental biofilm will be dispersed in the transport tube containing glass pearls through agitation at maximum speed in a vortex device for 30 seconds to homogenize the biological material. Next, the biofilm will be diluted in series on the order of 10^1^ to 10^6^ in peptone water and inoculated in culture media in Petri dishes. Aliquots of dilutions 10^4^, 10^5^, and 10^6^ will be sewn on the surface of Brucella agar (Difco, Kansas City) containing defibrinated sheep blood (50 ml/L), hemin (Inlab, São Paulo, Brazil) (5 mg/ml), and menadione (Inlab) (10 mg/ml) for the determination of the total number of viable microorganisms (VM). Aliquots of dilutions 10^3^ and 10^4^ will be sewn on Mitis Salivarius agar (Difco) for the determination of the total number of streptococcus (S). Aliquots of dilutions 10^1^ and 10^2^ will be sewn on Mitis Salivarius agar with the addition of debacitracin for the determination of the population of streptococcus of the mutans group (SM).^[34]^ Aliquots (100 μl) from each dilution will be sewn onto the surface of agar and spread with the aid of a Drigalski spatula. Undiluted aliquots and aliquots from dilution 10^2^ (100 μl) will be pour plated on Rogosa SL agar (Difco) for the determination of lactobacilli (LB)_._ The Brucella agar dishes will be incubated in an anaerobic chamber (PLAS by LABS, Lansing, MI) at 37°C for 7 days. The Mitis Salivarius agar and Mitis Salivarius Bacitracin dishes will be incubated in a 10% CO_2_ atmosphere (CO_2_ greenhouse, Shel Lab, mod. 2123, Oregon) at 37°C for 48 hours. The dishes containing Rogosa agar will be incubated in a 10% CO_2_ atmosphere at 37°C for 72 hours_._ After incubation, the characteristic colonies in each dish will be counted with the aid of a stereomicroscope at a magnification of 10 times in dilutions with 30 to 300 colonies per dish. All procedures will be performed in duplicate and the mean of the counts will be calculated. The results will be expressed in CFU of SM and LB as well as in proportion of streptococcus (% S/VM), SM group (% SM/VM and lactobacilli (% LB/VM) in relation to the total of VM. For SM, the proportion in relation to the total of streptococci (% SM/S) will also be calculated.^[37]^

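### The t test and ANOVA are assigned to reversible pulpitis, which no assessment records, while CFU, the outcome that sized the trial, gets no group comparison in the statistical analysis section

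*Protocol article*

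**What the plan says.** All references are to the protocol article.

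- **Statistical analysis (3.1.17)** works at the 5% level ("considering a 5% level of significance") and names three things: chi-square and Fisher tests for associations of categorical variables with age and gender; the Student t test and ANOVA, where "analysis of variance will be used for the comparison of means of the signs and symptoms of reversible pulpitis"; and Pearson correlations among continuous variables. The abstract repeats the pulpitis target.
- **Sample size (3.1.8)** takes its inputs from an earlier study, "considering the expected difference and standard deviation and weighting colony forming units (CFU) of bacteria". It adds: "For the statistical calculation, paired samples were considered". With 5% alpha "and an 80% test power", it arrives at 16 teeth per group.
- **Microbiological evaluation (3.1.12)** takes dentin before and after caries removal and cultures total viable microorganisms, streptococci, mutans streptococci and lactobacilli. On reporting: "The results will be expressed in CFU of SM and LB as well as in proportion of streptococcus (% S/VM", with the list continuing to three further ratios.
- **Radiographic evaluation (3.1.13)** assigns a mixed-effects model to optical density.
- **Clinical evaluation (3.1.16)**: "The criteria used of the evaluation will be the retention of the restorative material in the cavity and the occurrence of secondary caries".
- **Exclusion criteria (3.1.6)** rule out, among other things, "sign or symptom of pulp involvement, clinical impossibility of restoration".

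**The concern.** A statistics section should point its tests at outcomes the trial collects, and first at the outcome that fixed its size. Here the one test of means in 3.1.17 is aimed at a variable with no measurement behind it, and the sizing outcome is left without a comparison.

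Followed literally, the t test and ANOVA cannot be run. Someone must then decide how to compare CFU: which organism count, raw or log scale, paired or unpaired, with or without the pre-treatment sample. With 16 teeth per group and several organisms, those choices can change the answer, and nothing in the section prevents them from being made after the counts are known.

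**Working it through.** **1. Is reversible pulpitis measured anywhere?** The assessment sections in turn:

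| Section | What is recorded | Pulpitis item? |
|---|---|---|
| 3.1.12 Microbiological | Colony counts before and after treatment | No |
| 3.1.13 Radiographic | Optical density, visual reading and subtraction of the remaining dentin | No |
| 3.1.14 Time | Procedure duration, use of anesthesia | No |
| 3.1.15 Anesthesia and pain | Six-point face scale during the procedure | No |
| 3.1.16 Clinical | Restoration retention and secondary caries; codes 0 to 9 | No |

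This gives none of five. Two clinical codes come closest: 5 (further treatment given) and 6 (tooth absent). Neither records the reason, so a pulpal cause cannot be recovered from them.

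**2. Does CFU have a group comparison in 3.1.17?** Chi-square and Fisher tests there concern categorical variables with age and gender. The t test and ANOVA concern pulpitis. Pearson correlation measures association between continuous variables and does not compare groups. None is a comparison of CFU between groups or between before and after.

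**3. What did the sizing assume?** The 16 per group cannot be reproduced: the expected difference and SD are not in the text, and the two figures with the calculation are not shown. Working backwards with the stated 1.96 and 0.84:

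- Paired formula: n = (1.96 + 0.84)² / dz², so dz = √(7.84 / 16) = √0.49 = 0.70, where dz is the mean paired difference divided by its SD.
- Two-sample formula: n = 2 × (1.96 + 0.84)² / d², so d = √(15.68 / 16) = 0.99.

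These are implied values and cannot be checked against the source study. They show that the same 16 per group stands for different assumed effects depending on whether the analysis is paired. The CFU analysis therefore has to be stated and has to match the sizing.

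**4. Is the design settled enough to write a paired analysis?** Procedures (3.1.11) gives a second tooth in the same child the other treatment, so 32 teeth would come from 32 / 2 = 16 children. Radiographic evaluation (3.1.13) instead refers to 48 teeth in 48 patients, one per child. The two cannot both hold, and the CFU model depends on which does.

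**5. Which counts are reported?** Six results are listed: absolute CFU for mutans streptococci and for lactobacilli, plus four ratios (S/VM, SM/VM, LB/VM, SM/S). Total viable count is cultured but enters the list only as a denominator. Section 3.1.8 does not say which organism's count was used for sizing.

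**The case against.** The strongest defence is that this is a condensed article. A full plan may well name the CFU test, 3.1.17 speaks generally of different tests, and 3.1.8 already commits to a paired CFU basis. That stands to this extent: silence about a CFU test would be no finding by itself. But the section is not silent. It names a test and assigns it to a variable the trial does not record, and the abstract repeats it. The article also ties a method to an outcome where it chooses to, for optical density.

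It could be said that the face scale captures a pulpitis symptom. It is taken during the procedure, to judge the need for anesthesia, and is not offered as a pulpitis score.

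Several stronger readings are tempting but are not supported:

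- *Eligibility makes pulpitis impossible.* Exclusion at entry does not stop it arising after treatment. Only the missing follow-up measurement counts.
- *No other group comparison exists.* That holds for comparisons of means in 3.1.17, not for the document, because 3.1.13 plans a model for optical density.
- *The age and gender tests are empty between-group tests.* The text describes associations of categorical variables with age and gender, which can be examined when both treatments are given in one child.
- *The hypotheses make total viable count the primary endpoint.* Viable bacteria appear only in the null hypothesis, which already grants a reduction, so the count does not separate the two hypotheses.
- *A t test on raw CFU would have almost no power.* The plan proposes no such test, and the claim needs SDs and effects that the document does not give.

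**Conclusion.** The point holds as a mismatch between sections. The test of means in 3.1.17 and the abstract is aimed at an outcome recorded in none of the five assessment sections, while the outcome behind the 16 teeth per group has no group comparison in 3.1.17. It is wrong as written and should be corrected before the CFU results are examined.

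This rests on the text alone and needs no assumed effect or SD. No loss of power can be put on it, because the sizing inputs are not in the text. A reader might go further and infer that the trial's main question will go unanswered. That does not follow: the CFU data are collected before and after treatment, and a sound comparison can still be specified.

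**What to change.** 1. **Settle the design.** Reconcile two teeth per child (3.1.11) and 32 teeth (3.1.4) with 48 teeth in 48 patients (3.1.13).

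2. **Redirect the comparison of means**, in 3.1.17 and the abstract. If the same-child design is confirmed, for example: *Primary analysis: post-treatment log10 CFU, Group 2 versus Group 1, in a linear mixed model with treatment and baseline log10 CFU as fixed effects and child as a random effect, two-sided 5%.* If it proves to be one tooth per child, the child term drops out and the paired sizing must be revisited. State how samples without countable colonies enter the log scale.

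3. **Name the primary organism count in advance**, matching the count used for sizing. The other counts become secondary.

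4. **Report absolute total viable CFU** in 3.1.12 beside the mutans streptococci and lactobacilli counts and the ratios. This is an addition to reporting; it need not be the primary count.

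5. **Delete the pulpitis t test and ANOVA**, or record pulp signs yes/no per tooth at 3, 6 and 12 months and compare them with an exact paired test. With 16 pairs that comparison would be mainly descriptive: at least six discordant pairs, all in one direction, are needed to reach 5% (2 × 0.5⁶ = 0.031; with five, 2 × 0.5⁵ = 0.0625).

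The cost is the rewording of one section and a sentence in the abstract. Items 2 to 4 use cultures already planned. Item 5, if pulp signs are kept, adds one yes/no field per tooth at three existing visits.
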